#### Demographic Information and Health Related Questions

For descriptive purposes, the following participant socio-demographic characteristics, including sex (male/female), age, education level (illiterate, elementary, middle school, high school or above), marital status (married, never married, widowed, divorced), household income (<12000 RMB, 12000-19999 RMB, 20000-59999 RMB,  $\geq$  60000 RMB), and employment (yes/no) will be collected at baseline.

Health behaviors including smoking status (never, former, current), alcohol consumption (never/seldom, < once a month,  $\geq$  once a month, daytime napping (0, 1-60 minutes/day, over 60 minutes/day) will also be obtained at baseline.

Self-reported medical history, including hypertension, diabetes mellitus, asthma, coronary heart disease, chronic bronchitis/emphysema, psychiatric disorders, and

---

malignant tumors will be collected at baseline.

### **Adverse Events**

A surveillance form will be used to screen for adverse events (AEs) and serious adverse events at each assessment visit (see Appendix A). Serious, unexpected AEs that are related or are possibly related to the study will be reported to the Institutional Review Board (IRB) immediately.

### **Qualitative Interviews**

We will obtain oral consent from each participant prior to the beginning of each interview. All interview will be recorded and transcribed. We will use RE-AIM to identify the domains, including: (1)Reach, participant perception of the program recruitment process; (2)Efficacy, is the intervention benefits for improving health benefits, the impact of intervention on participants; (3)Adoption, participants' evaluation of the adoption of each intervention; (4)Implementation, participants' satisfaction with the intervention program as a whole; (5)Maintenance, participants' willingness to continue performing PA after the end of the intervention and their overall attitude toward PA before and after the intervention.

### **Outcomes**

Our primary outcome is the PA level of the participants. Our secondary outcomes include sedentary behavior, self-efficacy, self-regulation, cognitive function, night-time sleep quality, weight, percentage weight change, body mass index, percentage body fat, visceral fat, waist circumference, hip circumference, waist-to-hip ratio, waist-to-height ratio, and systolic and diastolic blood pressure.

---

## **Quality Assurance and Control**

Quality assurance and quality control are of paramount importance in a randomized controlled trial. Standardized protocols for all measurements have been developed, and adherence to the written protocols is of utmost importance. All data collection personnel will be certified as competent to make the required measurements by trained experts. The following is a summary of the quality assurance and control program:

### **1. Personnel**

Quality control of personnel is carried out in three main areas: a) Staff in surveys, interviews, and telephone counseling will be trained by professionals, with unified technical standards. b) Clear division of jobs, e.g. logistics during the investigation and coordination of personnel on site will be handled by different people. c) Responsibilities will be clearly defined, e.g. a person will be responsible for the safekeeping and storage of questionnaires.

### **2. Research Instruments**

a) The study proposes to use internationally recognized research methods and tools (such as the PASE) to ensure the quality of the data. b) Intervention materials (e.g. dissemination materials) are developed by a team member specializing in physical education and sport, in consultation with relevant experts and with reference to national and international standards, in order to ensure the correctness and traceability of knowledge.

### **3. Quality Management System**

a) Develop and implement a quality control program within the project team to ensure quality control at each key stage. b) Establish good external communication and feedback mechanisms with the team leaders of the peer groups and key figures of the villages to implement quality control.

---

## **Data Management and monitoring**

Face-to-face interviews will be conducted to collect data by eligible assessment team at baseline, 4 weeks, 8 weeks, 6 months, 12 months, and 24 months after the baseline. The collected data will be transferred from paper form to electronic record through data entry by study personnel. Standardized approaches will be used to ensure the high-quality of data. Selected project managers will build the electronic database. Confidentiality of the database will be protected by using password-protected computers. Only those designated by the project manager can access the data using the encrypted computers under the supervision of management. The staff are trained to comply with and use protected health information.

The study team will conduct monthly quality monitoring checks. The database will only be shared among the study team. Emails will be encrypted if data will be sent between the project staff, however, emails will be minimized.

---

## Sample Size Computation

Based on the prior PA intervention meta-analysis, the sample size required for each group was estimated to be about 90 with a power of 80%, an  $\alpha$  of 0.05, and assumed an effect size of 0.42. Because the randomization occurs at the village level, we need to consider the clustering effect.

The sample size (SS) for a clustered RCT is defined by equation (1):

$$SS_{\text{cluster RCT}} = SS_{\text{standard RCT}} \times DE \quad (1)$$

The design effect (DE) is obtained from equation (2):

$$DE = 1 + (n-1) \times ICC \quad (2)$$

$$\text{Where: } ICC = \frac{\sigma_{\text{between}}^2}{\sigma_{\text{between}}^2 + \sigma_{\text{within}}^2} \quad (3)$$

and  $n$  = cluster size (number of participants per cluster)

In equation (3),  $\sigma_{\text{between}}^2$  is the between-cluster variance for the outcome measure and  $\sigma_{\text{within}}^2$  is the within-cluster variance for the outcome measure.

We conducted a pilot study prior to the SAWA to calculate the DE. With a DE of 2.1, we will need a sample size of 189 ( $90 \times 2.1$ ) for each group after factoring in the cluster effects. Taking participation attrition into account, we will screen 20% more participants. Each group will have 227 participants, so the total sample size will be 454 participants for the two groups (intervention group and control group).

---

## **Data Analysis Plan**

### **1. Primary Analyses**

The primary aim will be to assess the PA level at 4 weeks, 8 weeks, 6 months, 12 months, and 24 months in the context of linear mixed model effects multilevel models. In this analysis, the intention-to-treat approach will be used. In addition to the intervention group, assessment time, and their interaction terms, the model may include individual-level (age, sex) variables as explanatory covariates. A random village intercept term is included to account for clustering by villages. The primary study hypothesis of SAWA will be tested based on a two-tailed significance level of 0.05.

Although substantial effort will be employed to minimize missing data, it is inevitable that some missing data will occur. Missing data are expected due to drop outs and missed visits. The PA level is a subject-level variable and missing assessments would influence tests relative to treatment-by-time interactions. The primary analysis described above will be conducted within each dataset using linear mixed effect models and employ restricted maximum likelihood using all available data. Results of datasets will be combined to produce final estimates for between-group comparisons. This approach assumes data are missing at random: the mechanism that gives rise to missing data relies on observed data only.

An intention-to-treat analysis that includes all randomized participants, regardless of the number of assessments obtained, will be conducted. The analytical plans are flexible and will be adapted as scientific perspectives are advanced.

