### **Outcomes**

Our primary outcome is the changes in leisure-time activity at 8 weeks. Our secondary outcomes include household activity, work-related activity, total PA, proportions of meeting WHO recommendations, leisure-time preferences, sedentary behavior, self-efficacy, self-regulation, self-rated health, cognitive function, night-time sleep quality, weight, percentage weight change, body mass index, percentage body fat, visceral fat, waist circumference, hip circumference, waist-to-hip ratio, waist-to-height ratio, and systolic and diastolic blood pressure at all assessment time, as well as the leisure-time activity at 4 weeks, 6 months, 12 months, and 24 months.

---

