## **Data Analysis Plan**

### **1. Primary Analyses**

The primary aim will be to assess the leisure-time activity level at 8 weeks in the context of linear mixed model effects multilevel models. In this analysis, the intention-to-treat approach will be used. In addition to the intervention group, assessment time, and their interaction terms, the model may include individual-level (age, sex) variables as explanatory covariates. A random village intercept term is included to account for clustering by villages. The primary study hypothesis of SAWA will be tested based on a two-tailed significance level of 0.05.

An intention-to-treat analysis that includes all randomized participants, regardless of the number of assessments obtained, will be conducted. The analytical plans are flexible and will be adapted as scientific perspectives are advanced.

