### **2. Secondary Analyses**

#### **a. Handling of missing data**

Although substantial effort will be employed to minimize missing data, it is inevitable that some missing data will occur. Missing data are expected due to drop outs and missed visits. The leisure-time activity level is a subject-level variable and missing assessments would influence tests relative to treatment-by-time interactions. The primary analysis described above will be conducted within each dataset using linear mixed effect models and employ restricted maximum likelihood using all available data. Results of datasets will be combined to produce final estimates for between-group comparisons. This approach assumes data are missing at random: the mechanism that gives rise to missing data relies on observed data only. To assess the sensitivity and robustness of the results, we will compare results of two sets of analyses: i) all participants, with or without missing data, were subjected to the repeated measures linear mixed model analysis; ii) we will perform the linear mixed model with missing

---

data imputed using multiple imputation.

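### The primary mixed model names no within-participant covariance, so it lacks the missing-at-random validity the plan states; drop-out whose link to activity differs by arm can bias the 8-week effect

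*Supplement*

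**What the plan says.** The final protocol (Outcomes) sets one primary endpoint: "Our primary outcome is the changes in leisure-time activity at 8 weeks". Its Data Analysis Plan, 1. Primary Analyses, gives the model. The fixed part is: "In addition to the intervention group, assessment time, and their interaction terms, the model may include individual-level (age, sex) variables as explanatory covariates". The random part is: "A random village intercept term is included to account for clustering by villages". No other random effect, residual covariance structure or baseline-activity covariate is named.

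Under 2. Secondary Analyses, a. Handling of missing data, the primary analysis is to "employ restricted maximum likelihood using all available data", followed by "This approach assumes data are missing at random: the mechanism that gives rise to missing data relies on observed data only". That sentence stands unchanged from the original protocol. The same paragraph says "Results of datasets will be combined to produce final estimates for between-group comparisons" without defining the datasets. It then adds a robustness comparison ("To assess the sensitivity and robustness of the results, we will compare results of two sets of analyses"): one analysis described as "all participants, with or without missing data, were subjected to the repeated measures linear mixed model analysis", the other the mixed model on multiply imputed data. The imputation predictors are not given.

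The secondary-outcomes section applies a similar strategy to the continuous secondary outcomes, with assessments out to 24 months.

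**The concern.** Likelihood-based estimation on all available data is valid under missing at random only if the model represents how observed and missing values are related. Here the relevant relation is between a participant's missing 8-week score and the same participant's baseline and 4-week scores. With a village intercept as the only random term, a participant's visits are independent given village, arm and visit. The earlier scores then carry next to no information about the missing one. The 8-week contrast becomes, in effect, those seen at 8 weeks minus everyone seen at baseline.

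That estimate is protected against drop-out unrelated to earlier activity, but not against the wider class of mechanisms that the plan says it covers. The issue is the point estimate, not only its standard error.

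Drop-out that works differently by arm is conceivable. Only intervention participants receive weekly calls about whether they met their goals, and only they belong to peer groups with shared goals. The documents do not show that it will happen.

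**Working it through.** **The plan's own figures (Sample Size Computation).** n per group = 2(1.96 + 0.8416)² / 0.42² = 89 (plan: about 90). 90 × 2.1 = 189; 189 × 1.2 = 226.8, so 227; 2 × 227 = 454. The plan's sample size reproduces. Two inputs follow from it:

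- Village ICC: (2.1 - 1)/(189/4 - 1) = 1.1/46.25 = 0.024.
- Loss, if the whole attrition allowance falls by week 8: 1 - 189/227 = 16.7%.

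**Assumed, because the documents do not give them.** Within-participant correlation ρ, the logit slope b of drop-out per SD of observed score, and how drop-out differs between arms.

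**Size by formula.** Let Z be the standardised 4-week score and p(Z) = 1/(1 + exp(-(c + bZ))) the chance of missing week 8, with c set so that the average loss is L. The mean 4-week score of those retained shifts by

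s = -b · E[p(1 - p)] / (1 - L).

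For b = -1 and L = 1/6, numerical integration gives E[p(1 - p)] = 0.1218, so s = 0.1218/0.8333 = 0.146. If only the intervention arm drops out this way, the village-only contrast is off by about ρ × s. For b = -0.5, -1, -1.5, s = 0.081, 0.146, 0.192.

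**Simulation of the same case.** 4 v 4 villages of 57, ICC 0.024, true effects 0, 0.30 and 0.42 SD at baseline, 4 and 8 weeks, 16.7% missing at week 8 (by 4-week score in the intervention arm, at random in control), 120 runs per cell, Monte Carlo SE about 0.004:

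| ρ | Formula, b = -0.5 / -1 / -1.5 | Simulated bias, village intercept only |
|---|---|---|
| 0.4 | 0.032 / 0.058 / 0.077 | 0.033 / 0.054 / 0.072 |
| 0.6 | 0.048 / 0.088 / 0.115 | 0.043 / 0.090 / 0.108 |
| 0.7 | 0.056 / 0.102 / 0.135 | 0.058 / 0.095 / 0.137 |

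The range is 0.03 to 0.14 SD, or 8% to 33% of 0.42. With a participant random intercept added, the bias lies between -0.004 and 0.003 in every cell.

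**Less loss by week 8.** The same formula over ρ 0.4 to 0.7 and b -0.5 to -1.5 gives 0.020 to 0.085 SD at 10% loss and 0.010 to 0.045 SD at 5%.

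**Other patterns of drop-out.** A second simulation used slope 1 per SD, one sixth lost, true effect 0.42 at 4 and 8 weeks, and 200 runs per cell (Monte Carlo SE 0.006 to 0.008). Mean village-only estimate:

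| Drop-out related to | ρ = 0.3 | 0.5 | 0.7 |
|---|---|---|---|
| nothing | 0.411 | 0.413 | 0.427 |
| low baseline, same in both arms | 0.427 | 0.432 | 0.422 |
| low 4-week score, same in both arms | 0.408 | 0.401 | 0.383 |
| low 4-week score, intervention arm only | 0.466 | 0.485 | 0.515 |
| opposite directions in the two arms | 0.499 | 0.550 | 0.612 |

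With the participant intercept, every cell lies between 0.410 and 0.428. The third row understates the effect by 3%, 5% and 9%. Fewer intervention participants are lost there because their 4-week scores are higher, so the arm shifts do not quite cancel. At b = -1.5 the formula puts that understatement at 0.021 to 0.048 SD for ρ 0.3 to 0.7.

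**The case against.** - **Silence is not specification.** The village term is described by its purpose, and the missing-data section calls the analysis repeated measures. The team may intend a participant term. That stands as a caution: the term is unnamed, not excluded. But the label fixes no covariance structure, and an analyst following the Primary Analyses section would fit the village intercept alone.
- **Multiple imputation is planned.** Imputation from earlier scores could restore the protection or expose a discrepancy, and the wording about combining datasets might even mean imputed data. However, imputation is presented as a robustness comparison, its predictors are not stated, and the datasets are undefined. It does not repair the primary analysis as written.
- **The outcome is a change.** If each participant's change were the response, the bias when the 4-week score drives loss would be (ρ - ρ) × s = 0 under constant within-person correlation. That is correct for this mechanism. But the Primary Analyses section speaks of level and includes assessment time. Change scores are not protected in general either: baseline-driven loss in one arm gives (ρ - 1) × s, which at b = -1 is -0.088 for ρ = 0.4 and -0.044 for ρ = 0.7.
- **The loss is placed at week 8.** The attrition allowance is not tied to that visit, and follow-up runs to 24 months. This stands; the bias at the primary endpoint may be well below the top of the range.
- **The arm difference is assumed.** This also stands. A reader might infer that any drop-out related to activity biases the 8-week effect, or that the trial will overstate it. The documents do not support either: drop-out tied to baseline equally in both arms gave no bias beyond simulation error, and a common link to the 4-week score gave a modest understatement.

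**Conclusion.** The point holds in a conditional form. As written, the primary model does not have the missing-at-random validity that the plan states, because nothing in it links a participant's visits. Whether the 8-week estimate is materially biased depends on drop-out being related to observed activity differently in the two arms.

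The 0.03 to 0.14 SD overstatement belongs to one assumed case, with loss driven by the 4-week score in the intervention arm only. It is an illustration of size, not a forecast. It also rests on reading the model as fitted to levels with no unstated participant term.

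This should be fixed rather than treated as a fatal flaw. It is more than missing detail, because the added term changes the answer under a mechanism that the plan says is covered.

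**What to change.** - In the final protocol's Primary Analyses, and so by reference for the continuous secondary outcomes, add to the village intercept either a participant random intercept nested in village or an unstructured within-participant covariance across visits.
- In the missing-data section, state that the imputation model uses arm, village and the participant's observed earlier scores, and define the datasets whose results are combined.
- If the model is to stay as it is, replace the missing-at-random sentence with one saying that, given arm, visit and village, drop-out is assumed unrelated to the participant's earlier scores.

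The cost is a few lines of analysis-plan wording and one extra model term, with no new data and no change to the conduct of the trial.

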### **2. Secondary Analyses**

#### **a. Compliance and As-Treated Analyses**

Two additional analyses will be conducted to compare intervention groups accounting for compliance with intervention protocol: i) restricted to only those participants treated

---

as specified by the random assignment, and ii) with assigned intervention replaced with actual treatment administered (provided accurate data on actual intervention modality can be obtained). The results of these analyses will be compared with the intent-to-treat analyses.

#### b. Secondary Outcomes

The secondary outcome data including sedentary behavior, self-efficacy, self-regulation, cognitive function, night-time sleep quality, weight, percentage weight change, body mass index, percentage body fat, visceral fat, waist circumference, hip circumference, waist-to-hip ratio, waist-to-height ratio, and systolic and diastolic blood pressure will be collected at the baseline, 4-week, 8-week, 6-month, 12-month, and 24-month follow-up. Generalized linear mixed models were used to test the effect of the intervention on the binary outcomes. For continuous outcomes, analyses will be performed using a similar strategy as the primary analyses.

### **3. Subgroup Analyses**

Modification of the effect of intervention upon primary and secondary outcomes will be performed separately in subgroups including age groups, sex, education level, household income, and BMI at baseline. Tests for key interactions (different intervention effects between sub-groups) will also be performed. However, it is recognized that the study may not be powered adequately to detect interactions; all subgroup analyses will be considered exploratory.

---

## **Trial Organization**

The Principal Investigator will oversee and monitor progress to reach the milestones with decisions concerning short-term goals and the evaluation of longer-term progress being discussed with the research staff via weekly meetings. The research team will be organized into sub-teams of investigators and staff. The overall organizational structure will be reviewed and amended as required.

### **Intervention Team**

The Intervention Director will lead the intervention team, which will consist of health psychology, health literacy, and physical activity experts who will develop the intervention materials.

### **Assessment Team**

The Assessment Director will lead the assessment team, which will consist of data collection technicians trained by the assessment director and experts in anthropometry, questionnaire administration and health literacy. The assessment team will be responsible for collecting data on the outcome measures at baseline, 4-week, 8-week, 6-month, 12-month, and 24-month visits.

### **Education Team**

The Director of Education and his/her team will be responsible for developing an educational program on PA for the intervention group in the trial.

---

## Timeline

The SAWA trial is designed as an 8-week intervention for rural older adults. The overall duration of the funding period of this study is three years. The following figure shows the timeline of activities (by quarter) for the SAWA trial.

| Activities                                  | 2020 |   |   |   | 2021 |   |   |   | 2022 |   |   |   |
|---------------------------------------------|------|---|---|---|------|---|---|---|------|---|---|---|
|                                             | 1    | 2 | 3 | 4 | 1    | 2 | 3 | 4 | 1    | 2 | 3 | 4 |
| Trial Registration                   |      |   |   |   |      |   |   |   |      |   |   |   |
| Pre-intervention Preparation         |      |   |   |   |      |   |   |   |      |   |   |   |
| Training of Outcomes Assessment Team |      |   |   |   |      |   |   |   |      |   |   |   |
| Participants Recruitment             |      |   |   |   |      |   |   |   |      |   |   |   |
| Intervention                         |      |   |   |   |      |   |   |   |      |   |   |   |
| Follow-up Visits                     |      |   |   |   |      |   |   |   |      |   |   |   |
| Data Analysis                        |      |   |   |   |      |   |   |   |      |   |   |   |
| Publications                         |      |   |   |   |      |   |   |   |      |   |   |   |

Figure 3. Timeline of Activities (by Quarter) for the SAWA Trial.

---

